Box 1ObjectivesStudy Identifier: clinicaltrial.gov identifier NCT05145803Objective 1: Identification of risk factors for, and rate of, infection in index cases and for transmission from index case to contacts.Objective 1.1: Describe demographics and evaluate risk factors for infection in index cases.Objective 1.2: Evaluate risk factors for transmission from index case to contacts (and their contacts), including viral load, clinical symptoms, vaccination status, activity and environmental metrics and immune response profiles (eg, neutralising antibodies, cytokine profiles—using a blood sample taken after recovery).Objective 1.3: Analyse the difference in the clinical status (symptomatic vs asymptomatic) for index cases as well as secondary cases by humoral and T-cell immune response profile (using the blood samples collected).Objective 1.4: Determine rate of and time to transmission, stratified by a variety of risk factors (including presence of clinical symptoms, activity and environmental metrics both in index cases and secondary contacts), analysing presymptomatic and asymptomatic exhalation of SARS-CoV-2 in contacts of index cases.Objective 2: In confirmed index cases and their contacts, quantify and determine the efficacy of the polyvinyl alcohol (PVA) test strip method for SARS-CoV-2 detection, comparing with the respective ‘reference standard’ (eg, nasal swab) collection method and correlating with the presence of antibodies.Objective 2.1: Assess the association between molecular detection by PVA test strip and molecular or antigen detection/quantification by initial reference diagnostic collection method.Objective 2.2: Assess the association between molecular detection by PVA test strip and molecular or antigen detection method (self-sampling) over the sampling/mask-wearing period.Objective 3: Due to the concern around emerging variants with higher transmissibility, carry out deep sequencing of PCR-positive samples (swabs as well as strips from masks) to derive the genotype of infecting virus.Objective 3.1: Share in timely fashion the results of the sequencing with the national/regional surveillance system.Objective 3.2: Assess the genetic similarities and differences of the SARS-CoV-2 variants by sequence comparison and by virological culture to assess cell-based infectivity of the strains.Objective 3.3: Determine the chain of transmission and relationship to clinical phenotype in the index case and contacts where viral RNA or culture permit.Objective 3.4: Analyse the difference in rate of transmission (see also objective 1) comparing different SARS-CoV-2 variants.

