
## Methods and analysis

### Study design

This is a prospective study with daily follow-up to capture early transmission in the presymptomatic phase. Index cases are identified by the routine testing system implemented at each participating institution and contacts of index cases are identified by the site-specific contact tracing system. The contact definition is based on CDC and the local health department guidelines (ie, individuals who are cohabitating or who were in close (<6 feet), extended (>15 min) contact with the index case and within 48 hours of diagnosis) and will be updated to reflect the most recent definition available. Study sites have an ongoing active case detection and contact tracing programme. Inclusion criteria and endpoints are described in box 2.

Box 2Key study design informationInclusion/exclusionInclusion criteriaIndex patients: Individuals aged≥18 years of any gender tested positive for SARS-CoV-2 by a molecular reference test (PCR test or antigen test).Contacts: Individuals aged≥18 years and known to be contacts of the index patients.Exclusion criteria: Age<18 years old, unable to wear a face mask due to underlying condition, unable to consent, pregnancy. In addition, signs of severe disease present at time of enrolment (eg, difficulty breathing, pain when breathing, tightness of chest or developing irregular heartbeat).EndpointsA. Outcome measure(s)Objective 1 outcomes: polyvinyl alcohol (PVA) strip positivity; nose swab test positivity.Objective 2 outcomes: PVA strip positivity and virus quantification (by PCR); nose swab test positivity; antigen test positivity; presence of antibodies in the blood.Objective 3 outcome: Deep sequencing of PCR-positive samples to derive the genotype of the infecting virus.

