### Schedule of wearing masks

Participants will be asked to wear a mask with two PVA test strips adhered to the inside surface for 2 hours per day. Index cases will complete 7 days of mask wearing and if they test positive by the end of the 7-day period, they will be asked to continue for another 7 days up to day 14. Contacts will complete 7 days of mask wearing as long as they test negative. If testing positive in the first 7 days, they will complete an additional 7 days of mask wearing starting with the day when they first test positive. If by the end of this period they still test positive, the duration will be extended by 2-day intervals with their permission until two consecutive masks wear dates test negative (figure 2). On completion of 2 hours of wear by the participant, the face masks will be placed in a sealed plastic bag, collected daily and brought into the laboratory where the PVA strips will be put into tubes with viral transport medium (VTM). The VTM tubes with the PVA strips will be eluted and tested by PCR.

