### Self-administered nasal swabs

We ask the participants to collect a self-administered nasal swab daily by placing a nasal swab approximately 0.5 inches into one nostril and swabbing the inside of the nose. The swab is then immediately placed into a 15 mL conical tube containing 2 mL of VTM. Samples are put into a separate sealed bag and stored at 4°C until testing.

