### Data analysis

For objective 1, we will first conduct a descriptive analysis of the index cases. Then we will conduct a risk factor analysis using multivariable multilevel regression models to determine symptoms and behaviours that are associated with greater exhalation of SARS-CoV-2 virus, as detected by PVA test strips. We will also analyse presence and timing of symptoms in contacts to determine if PVA strips can detect SARS-CoV-2 in exhaled breath of presymptomatic and asymptomatic individuals. We will map the transmission dynamics visually, determine the length of exhalation of SARS-CoV-2 in cases and calculate the difference in rate of transmission by vaccination status. Using the convalescent blood sample, we will analyse different immune response profiles (neutralising antibodies, T-cell-based assays) stratified by clinical phenotype (symptomatic/asymptomatic, potentially using a symptom score for increased granularity).

To address objective 2, we will calculate the sensitivity and specificity of the FMS method, using the initial reference diagnostic method of the site in index cases. We will then calculate the sensitivity and specificity of the PVA test strips using the concurrently collected nasal swab as the reference standard for both index cases and their contacts. We will also correlate strip test positivity with Ct value of the PCR test (or viral load in a subset) over time and with presence of antibodies (IgA and IgG) over time.

To address the concern about emergence of new virus variants, in objective 3, the FMS eluted materials, original specimen and/or recovered live virus isolates will be subjected to deep sequencing to monitor genetic variants in the study population. We will use these data, when available, to calculate the infectiousness of each viral variant and to map the transmission chains and association with disease in contacts. We will provide the sequence information of identified SARS-CoV-2 variants (and aliquot of material) to national and global data warehouses for public health surveillance of virus variation that may impact disease transmission and resistance to vaccines. The remaining materials will be stored for longer term so that they can be accessed for public health surveillance purposes.

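### Objective 2.1 scores strips in index cases against one earlier, always-positive diagnostic test with no stated time limit, so its sensitivity figure mixes strip performance with viral clearance and enrolment delay

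*Protocol article*

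**What the plan says.** The Data analysis section gives two accuracy analyses for objective 2. The first reads: "we will calculate the sensitivity and specificity of the FMS method, using the initial reference diagnostic method of the site in index cases". The second scores the strips "using the concurrently collected nasal swab as the reference standard for both index cases and their contacts". Box 1 has the same pair. Objective 2.1 is to "Assess the association between molecular detection by PVA test strip and molecular or antigen detection/quantification by initial reference diagnostic collection method", and objective 2.2 compares strips with self-sampling over the mask-wearing period.

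Three other places bear on the first analysis:

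- **Box 2, inclusion criteria.** An index patient is an adult who "tested positive for SARS-CoV-2 by a molecular reference test (PCR test or antigen test"). No maximum age of that result is stated. The only time limit nearby, "contact with the index case and within 48 hours of diagnosis", belongs to the definition of a contact.
- **Schedule of wearing masks.** "Index cases will complete 7 days of mask wearing and if they test positive by the end of the 7-day period", they are asked to go on to day 14.
- **Self-administered nasal swabs.** "We ask the participants to collect a self-administered nasal swab daily", so same-day pairs exist for index cases.

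The article does not say which mask or masks enter the comparison with the initial test.

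**The concern.** A sensitivity estimate needs the reference to describe the same state, at the same time, as the test under study. In objective 2.1 the reference is one past result, while the strip measures exhaled virus on a later day. The plan itself expects exhalation to stop, since it sets out to determine how long it lasts.

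Because the reference is positive for everyone in this analysis, every negative strip is classed as a false negative, including one that correctly shows that exhalation has ended. The qualifying test may be PCR or antigen and is whatever the site uses, so the meaning of reference-positive can also vary.

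What is at stake is a published sensitivity for a new sampling method. The section on the FMS method says this quantity is not yet conclusively determined and is part of the project. A reader could take the objective 2.1 figure as a property of the strip when part of it reflects how soon index cases were enrolled.

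**Working it through.** **The plan's own figures.** The Sample size section gives 300 index cases, about 10 contacts each and 5% transmission. 300 + 300 × 10 = 3300 and 300 × 10 × 0.05 = 150, so both stated totals reproduce. Neither concerns objective 2, for which the article states no sensitivity, precision or power figure.

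**What follows from the text alone.** In index cases the reference is positive by entry criterion. Hence apparent sensitivity = (positive strips) / (all strips scored), whatever the day. In the concurrent-swab analysis, a mask paired with a negative same-day swab leaves the sensitivity denominator, so clearance does not count against the strip.

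**How large the effect could be.** The documents give neither the clearance time nor the delay from specimen to first mask. All inputs below are assumptions, used to show a range.

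*Illustration A: a perfect strip with gradual clearance.* The share still shedding t days after the specimen is S(t) = exp(−ln 2 × (t/m)²), with median m. A first mask worn at lag L gives S(L). Scoring seven masks gives the mean of S(L) to S(L+6). For example, with m = 7 and L = 5, S(5) = exp(−0.693 × 25/49) = 0.702.

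| Assumed median m | Masks scored | Lag 0 days | Lag 2 days | Lag 5 days |
|---|---|---|---|---|
| 7 days | first only | 100% | 94.5% | 70.2% |
| 7 days | all seven | 84.5% | 69.0% | 42.1% |
| 14 days | first only | 100% | 98.6% | 91.5% |
| 14 days | all seven | 95.6% | 90.5% | 79.1% |

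*Illustration B: a strip with true same-day sensitivity s = 80% and a fixed shedding time.* Shedding continues D days after the test and the first mask is worn d days after it. Over seven masks, apparent sensitivity = s × max(0, min(7, D − d)) / 7. For D = 7 and d = 3 this is 0.8 × 4/7 = 46%.

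| D | d = 0 | d = 1 | d = 3 | d = 5 |
|---|---|---|---|---|
| 5 days | 57% | 46% | 23% | 0% |
| 7 days | 80% | 69% | 46% | 23% |
| 10 days | 80% | 80% | 80% | 57% |

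If only the first mask is scored, the result is s × (1 − q), where q is the share of index cases enrolled after shedding ended: 0.8 × 0.9 = 72% at q = 10%, and 0.8 × 0.7 = 56% at q = 30%.

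Both illustrations point the same way. Scoring only the first mask reduces the shortfall but does not remove it while the lag is unbounded.

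**A side observation.** The same sentence promises specificity. With no reference-negative index case in this comparison, specificity has no denominator there.

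**The case against.** The strongest reply is that the plan already contains the remedy: the next sentence of the Data analysis section scores the same index cases against a same-day swab, collected daily. That is correct. A reader might infer that the past test is the only yardstick for strips in index cases, and the text rules this out. It does not repair objective 2.1, which is a named objective and will produce a sensitivity figure of its own.

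A second reply is that the choice of mask and time window is detail that a journal article may leave to the full protocol or SAP. This also stands, so the silence on mask choice is not itself the point. A reader might infer that all masks are scored against the initial test, and hence that a loss on the scale of the seven-mask rows is to be expected. The text does not say so. Box 1 words objective 2.1 as an association and keeps it apart from the comparison over the mask-wearing period. What the article does fix is the reference standard, and that confounds strip performance with clearance even on the first-mask reading.

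Other tempting extensions lack support:

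- Days 8 to 14 are not an open-ended source of false misses. Index cases go past day 7 only if they still test positive.
- Nothing says that the length of exhalation is counted from enrolment. The questionnaire records the day of symptom onset, contacts are sampled before they turn positive, and a limit on time since diagnosis would not reveal when exhalation began in index cases.
- Differences between sites are possible, not established. No site's delay or test mix is given.
- Routine testing, active case detection and daily follow-up suggest prompt enrolment, though they set no limit.

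**Conclusion.** The point holds for objective 2.1 only. Its reference is a single earlier result that is positive by design, with no stated limit on the time to the mask. To the extent that masks worn after shedding ended are scored, the figure is too low as a measure of the strip, and it also reflects clearance, enrolment delay and the type of qualifying test.

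The size cannot be fixed from the documents. It ranges from no loss (first mask, no lag) to a large one (several masks, or late enrolment), and every percentage illustrated here rests on assumed clearance, lag and mask selection.

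Objective 2.2 does not have this problem and already gives an accuracy estimate in index cases. The study calls itself exploratory, so this is a worthwhile correction to one comparison. It does not undermine the evaluation of the strip as a whole and gives no reason to change who may enrol.

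**What to change.** Change the analysis text and leave the eligibility criteria as they are:

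1. Record the collection date of the diagnostic specimen for each index case.
2. Limit the comparison with the initial test to the first mask worn within a stated short window of that specimen, with the window's length set before the data are examined.
3. Report later masks as the proportion positive by day since specimen, stratified by PCR or antigen qualifying test, and do not call this sensitivity.
4. Name the concurrent-swab comparison as the accuracy estimate for the strip.

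The work is one date field and a few sentences. The downside is that fewer index cases enter objective 2.1, each with one mask. With all 300 index cases and an assumed sensitivity of 80%, the 95% half-width would be 1.96 × √(0.8 × 0.2/300) = 4.5 percentage points. If only half fell inside the window (an assumption), it would be 1.96 × √(0.8 × 0.2/150) = 6.4 points. The window reduces the timing effect but does not abolish it, which is why step 4 matters.

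### Using the same-day nasal swab as the reference for specificity in infected people counts true strip detections as false positives: a large bias among infected people, a small one when pooled

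*Protocol article*

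**What the plan says.** Under Data analysis, objective 2 has two accuracy analyses.

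- The first computes sensitivity and specificity of the face mask method "using the initial reference diagnostic method of the site in index cases". Box 2 (Study design) requires a positive PCR or antigen test for entry as an index case.
- The second computes sensitivity and specificity of the strips "using the concurrently collected nasal swab as the reference standard for both index cases and their contacts".

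The two samples differ in kind. The swab is self-taken by "placing a nasal swab approximately 0.5 inches into one nostril". For the strip, participants "wear a mask with two PVA test strips adhered to the inside surface for 2 hours per day".

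The objective 1 part of the same section uses timing of symptoms in contacts to "determine if PVA strips can detect SARS-CoV-2 in exhaled breath of presymptomatic and asymptomatic individuals".

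Antigen testing and virus culture of the strip eluate (Laboratory methods) and correlation with Ct value and antibodies over time (Data analysis) are also planned. None of these is used to define infection status in the specificity analysis.

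**The concern.** Specificity should describe how often the strip is negative when there is no virus to find. On a swab-negative day in a confirmed case, or in a contact who converts, that condition is not established. The person is or may be infected, and one shallow swab from one nostril can miss what two hours of exhaled breath picks up. If the strip is positive and right on such a day, the plan counts it as an error of the strip.

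The direction is fixed: true detections on swab-negative days can only lower apparent specificity. At stake is how the new sampling method is judged. Any additional or earlier detection it offers would be recorded as a fault, and a specificity quoted for index cases would mostly describe disagreement between two samples from infected people.

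**Working it through.** **Inputs from the document.** The Sample size section gives at most 300 index cases, about 10 contacts each and 5% transmission. Its figures reproduce: 300 × 10 × 0.05 = 150 secondary cases, and 300 + 3000 = 3300 participants. Under Schedule of wearing masks, "Index cases will complete 7 days of mask wearing", and contacts wear masks for 7 days while negative. The document states no expected specificity.

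**Step 1: the initial site test.** Index cases are positive on it by inclusion. Reference-negative index cases = 0, so specificity has a zero denominator. Only the same-day swab can supply one.

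**Step 2: person-days, taking 7 days per person.**
- Index cases: 300 × 7 = 2100
- Secondary cases: 150 × 7 = 1050
- Contacts never infected: 2850 × 7 = 19,950

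**Step 3: assumptions not in the document.** 30% of infected-person days are swab-negative; a share *f* = 10–20% of those are strip-positive; true strip specificity is 99.5%; swabs in uninfected contacts are always negative.

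**Step 4: results.**
- Swab-negative days in infected people: (2100 + 1050) × 0.30 = 945
- Strip-positive among them: 945 × 0.10 = 94.5 to 945 × 0.20 = 189
- Strip errors in uninfected contacts: 19,950 × 0.005 = 99.75
- All swab-negative days: 945 + 19,950 = 20,895

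| | *f* = 10% | *f* = 20% |
|---|---|---|
| Infected people only, 1 − *f* | 90% | 80% |
| Pooled false-positive rate | (94.5 + 99.75)/20,895 = 0.93% | (189 + 99.75)/20,895 = 1.38% |
| Pooled apparent specificity | 99.1% | 98.6% |
| Shortfall from 99.5% | 0.43 points | 0.88 points |

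**Step 5: wider range.** Let 10–40% of infected-person days be swab-negative and *f* run from 5% to 40%, with true specificity 100%.
- Among infected people, apparent specificity runs from 95% down to 60%.
- Pooled, the lowest loss is 315 × 0.05 / (315 + 19,950) = 0.08%, about 0.1 point.
- Pooled, the highest loss is 1260 × 0.40 / (1260 + 19,950) = 2.4 points.

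**Step 6: longer follow-up.** Seven days is a minimum for infected people, since the schedule extends wear for those who test positive. With 14 days each under the Step 3 assumptions, swab-negative infected days are 1890. The pooled false-positive rate is then (189 + 99.75)/21,840 = 1.3% to (378 + 99.75)/21,840 = 2.2%, a shortfall of 0.8–1.7 points, still inside the range in Step 5.

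**The case against.** Several points on the other side are sound.

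- **Pooled size.** Uninfected contact-days dominate, so the pooled loss is under one point in the base case. The article does not say that an index-only specificity will be reported. This stands.
- **Strip sensitivity.** The FMS method section puts the preliminary strip limit at Ct 18–20, whereas Laboratory methods calls samples positive below Ct 38. At face value the strip is the less sensitive sample, so strip-positive, swab-negative days may be uncommon and *f* may be low. This stands. It also means that nothing in the document shows such a day to be more likely a true detection than a strip error.
- **Conflict with objective 1.** A reader might infer that objectives 1 and 2 contradict each other, with presymptomatic detection a success in one and an error in the other. The text does not support that. Presymptomatic is defined there by symptoms, not by swab timing, and a presymptomatic day with both samples positive counts as a success under both objectives. Only days on which the strip turns positive before the swab are affected, and the document does not name these as the target.
- **Other evidence and unseen detail.** Antigen test, culture, Ct value and antibodies are planned, Box 1 words objectives 2.1 and 2.2 as association, and rules for discordant results may sit in the full protocol or analysis plan. That is fair, but the choice of reference is stated in the article, and it is the choice that creates the bias.
- **Relabelling.** Percent agreement equals sensitivity and specificity against the swab numerically. True, so a change of name is not enough: specificity has to come from a different set of people.

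These points limit the size of the bias. None reverses its direction.

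**Conclusion.** The concern holds as a downward bias built into the stated analysis. No printed figure is wrong. Under the assumed rates (30% swab-negative, 10–20% of those strip-positive, true specificity 99.5%), apparent specificity is about 80–90% among infected people, and about 0.4–0.9 points too low when pooled. None of these rates comes from the document, and the Ct 18–20 limit points to the lower end or below.

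A reader might also infer serious damage from the share of apparent false positives that infected people contribute: 94.5/194.25 = 49% to 189/288.75 = 65% here. That share is large only because errors in uninfected contacts are assumed rare. It does not make the pooled specificity badly wrong. The study is described as exploratory, and the swab remains a reasonable comparator. The problem is using it day by day to define specificity in infected people.

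**What to change.** 1. Estimate specificity from contacts who stay swab-negative throughout follow-up.
2. Drop specificity against the initial site test in index cases, since it cannot be computed.
3. For index cases and converting contacts, report same-day positive and negative percent agreement separately, with the full discordant table, and do not call it specificity.
4. If strip timing relative to the first positive swab is examined, describe it symmetrically: strip first, same day, swab first, and strip-negative days before conversion. Do not reclassify only the strip-positive, swab-negative days using later swabs. That is one-sided discrepant resolution and can only favour the strip.
5. Keep the pooled same-day table as supporting.

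The data are already collected, so the cost is wording and one extra table. The downside is that some never-positive contacts may be infections the swab missed, which leaves a residual downward bias in the new estimate.
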